## Abstract

**Background:**

Acute lower respiratory infections (ALRI) are a leading cause of death among children. Low birthweight is prevalent in South Asia and associated with increased risks of mortality, and morbidity, high levels of indoor household air pollution caused by open burning of biomass fuels are common and associated with high rates of ALRI and low birthweight. Alternative stove designs that burn biomass fuel more efficiently have been proposed as one method for reducing these high exposures and lowering rates of these disorders. We designed two randomized trials to test this hypothesis.

**Methods/design:**

We conducted a pair of community-based, randomized trials of alternative cookstove installation in a rural district in southern Nepal. Phase one was a cluster randomized, modified step-wedge design using an alternative biomass stove with a chimney. A pre-installation period of morbidity assessment and household environmental assessment was conducted for six months in all households. This was followed by a one year step-wedge phase with 12 monthly steps for clusters of households to receive the alternative stove. The timing of alternative stove introduction was randomized. This step-wedge phase was followed in all households by another six month follow-up phase. Eligibility criteria for phase one included household informed consent, the presence of a married woman of reproductive age (15–30 yrs) or a child < 36 months. Children were followed until 36 months of age or the end of the trial. Pregnancies were identified and followed until completion or end of the trial. Phase two was an individually randomized trial of the same alternative biomass stove versus liquid propane gas stove in a subset of households that participated in phase one. Follow-up for phase two was 12 months following stove installation. Eligibility criteria included the same components as phase one except children were only enrolled for morbidity follow-up if they were less than 24 months.

The primary outcomes included: incidence of ALRI in children and birthweight.

**Discussion:**

We presented the design and methods of two randomized trials of alternative cookstoves on rates of ALRI and birthweight.

**Trial registration:**

Clinicaltrials.gov (NCT00786877, Nov. 5, 2008).

## Background

Acute lower respiratory infections (ALRI) remain a leading cause of death among children in the developing world with the highest risk among the youngest children [1]. Small size at birth, including low birthweight (LBW) is also common and an important risk factor for early infant death with 28% of all neonatal deaths attributable directly to this condition [2]. Over the past few decades, there has been an increasing focus on the role of environmental exposures in the etiology or exacerbation of ALRI. In the mid-1950s in London, thousands of excess deaths, especially among young children and the elderly, were associated with extensive outdoor particulate air pollution due to smoke from coal burning household stoves [3]. More recent studies of outdoor air pollution have confirmed that respirable particulate exposure, even at the relatively low levels now seen in high-income settings, can increase respiratory mortality and morbidity [4–6]. While outdoor exposures in low- and middle-income countries play a role in the incidence and severity of respiratory disease [7], outdoor exposures are most extreme in urban environments and the vast majority of the studies on outdoor air pollution from developing countries have been done in these settings. Of more concern in rural areas is indoor air pollution where particulate matter concentrations can be many times those found outdoors [8]. Such high levels are particularly frequent in south Asia where biomass materials (dung, wood, and crop residue) are the predominant sources of fuel used for cooking and heating and where typical houses have limited ventilation and use open stoves without flues. It is not uncommon to observe concentrations between 2,000 and 15,000 μg/m^3^ during cooking [8–10], but very high exposures can continue throughout the day if the stove is also used for heat or the family prepares food items for sale. The observational epidemiological literature on the association of indoor smoke exposure and ALRI in young children demonstrates that exposure to incomplete combustion of biomass fuels increases by 2–12 fold the risk of respiratory symptoms or disease in preschool age children [11].

It is well known that certain particulate matter and other chemical respiratory exposures can cause reduced birthweight, intra-uterine growth restriction (IUGR), and preterm birth; the best examples being active and passive tobacco smoke exposure during pregnancy [12]. The observational evidence on the association between indoor air pollution and infant birth outcomes suggests that exposure to biomass fuel smoke is associated with a 97 g reduction in birthweight but the depth and quality of this literature varies substantially [13].

Other chronic disease outcomes are also associated with poor indoor air quality and the global burden of illness due to indoor burning of biomass fuels in 2010 has been recently estimated at 4.3% of all disability adjusted life years (DALYs) [14]. Use of cookstoves that utilize alternate fuels or incorporate a chimney for ventilation may reduce exposure and thus improve outcomes, but neither the exposure reduction nor the concomitant health gains have been adequately studied at the population level. We have implemented trials in rural Nepal to examine these questions, and present here the design of those trials.

## Methods

### Design

The Nepal Cookstove Intervention Project is a pair of randomized trials to evaluate the impact of using alternative cookstoves to improve indoor air quality, respiratory morbidity in young children, and reproductive outcomes in a population where indoor open burning of biomass fuels sources are the norm. The study was initially designed as a single trial with two identical cohorts, but after examining the exposure reduction performance of the alternative stove used in the first trial, it was decided to alter the second phase to a separate, but complementary randomized trial.

Phase One: This was a cluster-randomized, modified step-wedge trial (Figure 1). The study area was initially divided into 51 sectors of 20–30 households that were each estimated to provide between 25 and 40 children < 36 months of age. These sectors served as units for concurrent installation by a single stove installation team of the alternate biomass stove over a one month period. Sectors were then combined into 12 groups that served as the unit of randomization and corresponded to the 12 months of the step-wedge portion of the design. Within a group, sectors were geographically spread across the study area using a stratified systematic sampling procedure in order to prevent an additional level of clustering and within group correlation of the primary outcomes.

**Figure 1 Fig1:**
[figure not shown]
**Trials design scheme.**

This standard step-wedge design was modified by adding a six month period of outcome assessment in all groups prior to the start of the step-wedge and a similar six month period of outcome assessment following completion of the 12 month step wedge. This provided additional person-time and balance on season both before and after new stove installation. All three primary outcomes show marked seasonality in this population [15, 16].

Phase Two: The design of phase two was an individually randomized trial at the household level (Figure 1). Eligible households that participated in phase one and newly eligible households that did not participate in phase one were randomized to either an alternate biomass stove with chimney or a LPG stove with gas tank and 12 month supply. Follow-up of phase two was for 12 months following stove installation.

### Study population

The study population for Phase 1 consists of residents of all households in four Village Development Committees (VDCs) in Sarlahi District in the terai region of southern Nepal. The study population for Phase 2 included only households in 2 of these VDCs. The terai lies along the border with north India and is part of the flood plain of the Ganges River and its tributaries that drain from the Himalayas to the Bay of Bengal. This is not a high mountain area, but one characterized as low and flat (approximately 600 ft. elevation) with high population density. It is typical of most of northern India and large parts of western Bangladesh and northern and central Pakistan with a population of over one billion. It is predominately an area of traditional, rural, Hindu culture. The population is mostly peasant farmers (58%) or laborers (26%) and their families, and is considered a poor area, even in Nepal. It is an extremely poor environment with a per capita income of $146 [17].

### Household eligibility phase 1

Households were eligible for participation in the first trial if they:
● Did not currently have an improved, ventilated biomass cookstove, LPG cookstove or electric cookstove in the household.● Used their traditional open burning biomass cookstove indoors or in an area contained by at least 3 walls.● Had household walls of mud, brick, cement, or wood. Thatch or bamboo walled houses that were not plastered with mud were not eligible for fire safety reasons.● Were willing to have us install an alternative, ventilated biomass cookstove and be willing to use it for at least 12 months.● Have a married woman 15–30 years of age or at least one child <36 months of age residing in the household at the time of trial initiation.

### Household eligibility phase 2

Households were eligible for participation in the second trial if they:
● Resided in two of the original four VDCs from the Phase 1 trial.● Participated in the first trial and continued to have a married woman age 15–30 years of age or at least one child <24 months of age residing in the household at the initiation of Phase 2.● Were a new household in the study VDCs that had at least one married woman age 15–30 years of age or at least one child <24 months of age residing in the household at the initiation of Phase 2.● Were willing to be randomized to either continuing with their alternative, ventilated biomass stove from Phase 1 or to an LPG stove and to use it for 12 months.

### Intervention

Phase 1: The cookstove intervention in the first phase consisted of replacing the household’s traditional open burning stove with a commercially available two burner biomass stove with a chimney outlet and a chimney constructed from sheet metal. The stove used was model G-3300 with the G-3355 two pot attachment manufactured by Envirofit International (Colorado Springs, CO, USA) (Figure 2). Chimney pieces were manufactured by a local sheet metal firm and installed on-site by project stove installation teams. In addition to the provision of a new stove, extensive training and demonstration in the use and maintenance of the stoves was conducted and reinforced regularly throughout the follow-up period by a special team of stove monitors***.***

**Figure 2 Fig2:**
[figure not shown]
**Alternative biomass cookstove used in both trials.**

Phase Two: The cookstove intervention in phase two consisted of either, the continued placement and support for use of the alternate biomass stove (Envirofit model G-3300 + G-3355 with chimney), or the installation of an LPG two-burner stove with gas tank and adequate LPG supply for 12 months. The LPG stoves were manufactured in India and the LPG was sourced from one of three suppliers in Nepal and distributed monthly. All households who were randomized to the improved biomass stove arm were provided with a LPG stove, gas tank, and one month of LPG fuel at the end of the study.

### Primary and secondary outcomes

Primary outcomes for both trials included:Incidence of ALRI among children < 36 months of age. An episode of ALRI was defined as two or more consecutive days with maternal report of fever and fast/difficult breathing with both symptoms reported on at least one day during the episode and during which at least one symptom occurred each day. Consecutive episodes had to be separated by a minimum of 7 symptom free days. An episode of severe ALRI was defined as an episode of ALRI plus one or more of the following:● •respiratory rate >50 if the child was 12 months or older; >60 if the child was younger than 12 months;● •chest retractions;● •unconsciousness;● •chest auscultation finding of crackles in at least one quadrant.

Respiratory morbidity was assessed during weekly household visits where mothers or other caregivers were asked about signs and symptoms on each day in the preceding week. Maternal report of signs and symptoms included high fever, persistent cough, fast or difficult breathing, wheezing, watery stool, ear discharge, and burn injury. We also asked whether the child had been taken for care and where the child was taken. If a child had an episode of fast/difficult breathing in the past week, a separate visit was scheduled for examination as soon as possible by a more senior staff member to assess the child for danger signs, measure respiratory rate, oxygen saturation and conduct digital chest auscultation.2.Birthweight as measured by study staff using digital infant scales (Tanita Corp., Tokyo, Japan).3.Gestational age as measured by the start of last menstrual period.

Secondary outcomes for both trials included:Forced expiratory volumes among married women 15–30 years of age and one other randomly selected adult (15 yrs or older) member of the household. Forced expiratory volume in one second (FEV_1_) and forced expiratory volume in six seconds (FEV_6_) were measured using the Piko-6 pocket spirometer (nSpire Health, Longmont, CO, USA) and a disposable mouthpiece under a standardized protocol.Respiratory symptoms as assessed using a modified version of a standardized questionnaire [18] among married women 15–30 years of age and one other randomly selected adult (15 yrs or older) member of the household.Blood pressure and pulse among married women 15–30 years of age and one other randomly selected adult (15 yrs or older) member of the household. Blood pressure was measured using an automated osscilometric device (BpTrue 300, VSM MedTech Ltd, Coquitlam, Canada).Oxygen saturation, carboxyhemoglobin level, and heart rate during pregnancy using a pulse oximeter (Rad-57. Masimo Corp., Irvine, CA).Indoor air concentrations of respirable particulates (PM_2.5_) and carbon monoxide (CO).

### Randomization

Phase One: Randomization of the 12 groups to the timing of new stove installation was conducted in the project office in Kathmandu and was a transparent process with participation of senior field representatives. The numbers 1 through 12 were written on separate slips of paper and senior Nepal-based project staff drew slips one at a time out of a hat with the first group selected being the group that would have their stoves replaced in the first month, the second group selected having stoves replaced in the second month, etc.

Phase Two: Eligible households in phase two were individually randomized stratified by VDC and Ward using the sample procedure in STATA (StataCorp LP, College Station, TX). Households that had participated in phase one were randomized separately from newly eligible households.

### Data collection

The timing of data collection activities is outlined in Table 1 and described in more detail below.

**Table 1 Tab1:** **Data collection schedule**

	Household enrollment	Pregnancy enrollment	Monthly during pregnancy	Day of birth	One week post-partum	Weekly	Monthly	6 Monthly	End of follow-up
Household roster	**X**								
Household SES & characteristics	**X**								
Pregnancy surveillance							**X**		
Pregnancy history & maternal anthropometry		**X**							
Maternal morbidity		**X**	**X**						
Maternal Blood Pressure		**X**	**X**	**X**	**X**				
Maternal carboxyHb, O_2_ saturation & pulse		**X**	**X**						
Birthweight				**X**					
Child anthropometry	**X**							**X**	
Child vital status				**X**		**X**			
Morbidity						**X**			
Danger signs						**X** ^*****^			
Temperature						**X** ^*****^			
Respiratory rate & O_2_ saturation, pulse						**X** ^*****^			
Chest Auscultation						**X** ^*****^			
Adult Respiratory Symptoms & FEV1 and FEV6	**X**								**X**
Compliance with new stove use						**X**			

*For children receiving ALRI case examination.

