### Household census

A census of all households in the study area was conducted as a part of phase 1 in order to identify all eligible households for recruitment, obtain informed consent for participation, address eligible households for ease of identification during the data collection phase, and to collect basic information about residents of eligible households. A full household roster was collected and included identifying information, age, date of birth, sex, marital status, literacy, years of education, occupation, tobacco use, weight, height (length for children < 2 yrs), and individual consent status for all household residents. For married women 15–30 yrs and one randomly selected other adult (≥15 yrs), the following additional measurements were collected: FEV_1_, FEV_6_, blood pressure, and heart rate. These people also completed a respiratory symptoms questionnaire.

Assessment of household characteristics was collected for all eligible consented households. Variables collected included measures of household socioeconomic status using an asset index, ethnicity, number and types of cookstoves, house construction materials and size, source of drinking water, household sanitation practices, and whether there were members of the household working outside the local area or country (as a measure of additional cash income).

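### In phase one, adult FEV1, FEV6 and respiratory symptoms are scheduled only before any group has the stove and after all groups do, so the stove effect on them is confounded with occasion

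*Protocol article*

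**What the plan says.** The outcome list in the protocol article opens its secondary outcomes with "Secondary outcomes for both trials included:Forced expiratory volumes among married women 15–30 years of age and one other randomly selected adult". It continues with "Respiratory symptoms as assessed using a modified version of a standardized questionnaire", taken in the same adults. Both are therefore outcomes of phase one as well as phase two.

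Table 1 has one row for these measures, "Adult Respiratory Symptoms & FEV1 and FEV6". It is marked under household enrollment and under end of follow-up and nowhere else. The table has a six-monthly column, used for child anthropometry, but it is blank for adults. The Household census section confirms the first reading: for the selected adults, "the following additional measurements were collected: FEV_1_, FEV_6_, blood pressure, and heart rate", together with the symptom questionnaire.

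The phase-one timeline is given in the Abstract and the Design section. A household was eligible only if it "Did not currently have an improved, ventilated biomass cookstove, LPG cookstove or electric cookstove in the household". The standard design was modified by "adding a six month period of outcome assessment in all groups prior to the start of the step-wedge". Twelve monthly installation steps come next. Then, in the Abstract's words, "This step-wedge phase was followed in all households by another six month follow-up phase". Only the month of installation is randomised, across 12 groups.

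**The concern.** A stepped wedge yields a randomised stove effect because, during the steps, some groups have the stove and others do not at the same calendar time. Outcomes read throughout the steps use that concurrent comparison. An outcome read once before the first step and once after the last does not.

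A change in FEV1, FEV6 or symptoms between those two readings mixes the stove with everything else that changed over about two years. That includes ageing or growth in women aged 15 to 30, familiarity with spirometry at a second attempt, drift in the device, any seasonal mismatch between the visits, and secular change in respiratory illness.

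The article recognises the hazard elsewhere. Its Exposure modeling section warns that comparing the year after installation with the year before is open to bias from secular trend. Its Sample size section reports strong bias when a sizeable trend is left out of the model. For the adult outcomes, the schedule removes the means of separating the two. At stake is whether phase one can say anything causal about adult lung function and symptoms with versus without the stove.

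**Working it through.** The article gives no power or detectable difference for the adult outcomes, so there is no stated figure to reproduce. The check is whether the stove effect is identifiable.

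**Inputs**
- 12 randomised groups, with timing of installation randomised (Randomization).
- 6 months before the steps, 12 monthly steps, 6 months after (Abstract; Design): 6 + 12 + 6 = 24 months.
- Group g (g = 1 to 12) is installed during study month 6 + g, that is, months 7 to 18.
- Adult readings at month 0 and month 24 (Table 1, taking end of follow-up as the end of phase one).

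**Stove status at each reading**

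| Reading | Groups with stove | Occasion indicator T | Stove indicator X |
|---|---|---|---|
| Month 0 | 0 of 12 | 0 | 0 in every group |
| Month 24 | 12 of 12 | 1 | 1 in every group |

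So X = T, with correlation 1.0.

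**Consequence in the model.** With group effects a_g, occasion effect b and stove effect θ:

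E(Y) = a_g + b·T + θ·X = a_g + (b + θ)·T.

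Only the sum b + θ can be estimated.

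**Rank check**
- Two readings, fixed group effects: 12 group columns + 1 occasion + 1 stove = 14 columns. The rank is 13, and it is still 13 without the stove column. θ is not estimable.
- Two readings, random group effects: the fixed part has intercept, occasion and stove = 3 columns. The rank is 2. θ is not estimable.
- For contrast, 25 monthly readings (months 0 to 24): 12 + 24 + 1 = 37 columns. The rank is 37, against 36 without the stove column. θ is estimable.

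The loss comes from the timing of the readings, not from the stepped wedge or the number of adults.

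**What randomisation still provides.** Length of use at month 24, counted from the end of the installation month, is d_g = 24 − (6 + g) = 18 − g, giving 17, 16, …, 6 months, with mean 11.5. Counting the installation month as well gives 18 to 7.
- First six groups: mean of 17 to 12 = 14.5 (15.5 counted inclusively).
- Last six groups: mean of 11 to 6 = 8.5 (9.5 counted inclusively).
- Difference: 6.0 months on either count.

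A model with intercept, occasion and length of use has rank 3 of 3 columns, so a gradient in length of use can be estimated. Adding a stove on/off column leaves the rank at 3 of 4. No group has zero use at the final visit, so the gradient reaches a no-stove value only by extrapolation.

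**The case against.** The best case against the point is that this is a condensed article, that installation month was randomised, that these outcomes are secondary, and that phase two is a parallel-arm trial.

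- **Condensation.** The article applies its stepped-wedge model to ALRI and birthweight only. It states no adult analysis and claims no adult stove effect. A reader might infer that the plan commits to reporting a randomised phase-one stove effect on lung function; the text does not say that. But Table 1 is a positive statement of timing, and no later analysis plan can recover a contrast that was not sampled.
- **Randomised timing.** A reader might infer that randomisation contributes nothing to the phase-one adult outcomes. That goes too far: the length-of-use comparison is randomised. Only the on/off contrast is lost.
- **Phase two.** Its comparison of arms is randomised and free of this problem. It compares the alternative biomass stove with LPG, however, so it cannot stand in for traditional versus alternative stove.
- **Blood pressure and pulse.** Table 1 has no general-adult row for them, and a reader might infer that they were never read after the census. The documents do not support this, because Table 1 is not exhaustive. It also omits the census blood pressure reading and the household air monitoring before and after installation, both of which the text describes. The single adult row may stand for the whole adult visit.
- **Undated final visit.** Table 1 serves both trials and does not date the end of follow-up. For phase one, the natural reading is the end of the last six-month period. Any later date still falls after every group's scheduled installation.

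**Conclusion.** The point holds for adult FEV1, FEV6 and respiratory symptoms in phase one. On the schedule as printed, the effect of having versus not having the stove is completely confounded with measurement occasion and cannot be estimated as a randomised contrast at any sample size. What remains is an uncontrolled before-after change over about 24 months, plus a randomised length-of-use comparison whose early and late halves differ by 6 months on average.

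This assumes that Table 1 gives all the adult spirometry and symptom readings, that end of follow-up falls after the last step, and that groups were installed as scheduled. If some households missed installation, comparing them with the rest would not be randomised either.

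Severity is moderate. ALRI, read weekly, and birthweight, read at birth, are observed through the steps and are unaffected. So is the phase-two comparison.

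**What to change.** 1. State that the phase-one before-after change in FEV1, FEV6 and respiratory symptoms is uncontrolled, and make no randomised stove-effect claim from it.
2. As the only randomised phase-one analysis of these outcomes, regress the end-of-follow-up value on randomised installation month, adjusting for the enrollment value and allowing for clustering. Describe it as a length-of-use comparison, not as stove versus no stove.
3. Describe the phase-two adult result as alternative biomass versus LPG only.
4. Reconcile Table 1 with the outcome list and the Household census section on when adult blood pressure and pulse were read. If they were read only at the same two visits, the same limitation and wording apply.

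The cost is one extra model, some wording and a weaker phase-one adult claim.

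An adult reading midway through the steps would have given a concurrent comparison, with about half the groups installed. It would have been a trade-off: if it replaced the final visit, the longest-use readings would be lost, and use would be at most about six months. The article expects results in late 2014 or early 2015, so rescheduling is probably no longer possible.
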